#### Standard ART Counseling

All participants will receive one-on-one, in-person counseling at a clinic concerning the behavioral, psychosocial, and medical implications of HIV. This standard counseling session will last approximately 30 minutes. Health care providers connect newly diagnosed individuals to a range of services, including substance use treatment, mental health care, reproductive counseling, risk-reduction interventions, case management, and partner services. Clients also receive counseling on ART adherence and the management of treatment-related side effects.

## Methods

### Study Setting

Young people with HIV will be recruited from 2 large HIV clinics in Lusaka Province to ensure sample diversity. Lusaka is home to 3.4 million people (18.8% of Zambia’s population) [39] and has high HIV rates and high phone ownership among youth [40]. The Kanyama First Level Hospital (KFLH) serves a population of approximately 120,000 individuals aged 10 to 29 years in a high-density, low-income township near Lusaka [41]. The Matero Urban Health Centre (MUHC) is located in urban Lusaka and serves a population of 247,451 [41]. We will recruit young people with HIV from a broad range of socioeconomic backgrounds. MUHC typically serves middle- to higher-income families, whereas KFLH primarily serves lower-income communities. Together, these clinics provide access to diverse youth populations with substantial HIV burden and co-occurring substance use.

### Study Design

There are 3 phases in the study: phase 1 (formative research), phase 2 (intervention adaptation), and phase 3 (pilot randomized controlled trial [RCT]).

#### Phase 1: Formative Research

##### Overview

The first phase of the assessment, decision, adaptation, production, topical experts-integration, training, testing framework [42] is a needs assessment of the target population to guide cultural and developmental tailoring through 6 focus groups with young people with HIV in Lusaka. Focus groups are commonly used to inform intervention adaptation for young people with HIV in Africa, including Lusaka [43]. Cultural adaptation will be led by the Zambian and US investigators, who have expertise in working with young people with HIV, substance use, and mHealth intervention adaptation. We will conduct separate focus groups for male- and female-identifying young people with HIV (3 each), with 6 to 8 participants per group, using best practices for youth [44]. Focus group guides will be developed by the study team and structured around the IMB model. Topics will include knowledge about HIV self-management and substance use (information); attitudes toward ART, risk perceptions, and reasons for taking ART and attending appointments (motivation); and facilitators or barriers to ART adherence, appointment attendance, , and substance use (behavioral skills). We will also explore social supports, past successes, and strategies for overcoming barriers. Responses will be used to inform intervention content and delivery, including privacy concerns, disclosure, and acceptable session length. Participants will be recruited from MUHC (N=20) and KFLH (N=20) using purposive sampling to ensure representation. Focus groups will be audiotaped, transcribed, and will last approximately 1 to 1.5 hours.

##### CAB

A CAB of key stakeholders will be identified and assembled by the Zambia investigators, who have developed strong relationships with health care providers serving young people with HIV in Lusaka through years of HIV research. The CAB will include 4 young people with HIV, 4 Zambian health personnel (physicians, nurses, or other personnel engaged in direct care of young people with HIV), and 2 community leaders (eg, people living with HIV, advocates, nongovernmental organization representatives, or HIV researchers). Members will meet quarterly, with additional meetings as needed. The CAB will provide iterative feedback on HC and MTM intervention content, study materials, recruitment and retention strategies, privacy, stigma, cultural relevance, and implementation procedures for young people with HIV in Zambia. The first meeting will establish CAB functions and procedures consistent with community-based participatory research principles. Any inconsistencies in feedback will be resolved during meetings or, if needed, through discussion with the Zambia-US study team. Detailed notes will be taken during meetings. Study materials and intervention approaches will be revised based on the CAB’s feedback.

#### Phase 2: Adapting and Refining Motivational Enhancement System for Preexposure Prophylaxis Uptake and Adherence and MTM

##### Adapting HC for mHealth to Target Self-Management of HIV and Substance Use

Formative research will provide rich data on substance use and HIV self-management among young people with HIV within the Zambian cultural context and inform intervention development. We will use an established approach that progresses from formative research to pilot adaptation and RCT testing, guided by a framework for HIV interventions. The intervention flow is based on MI and progresses from exploration of the importance of target behaviors and confidence in these behaviors to goal setting. Participants will explore ambivalence around HIV self-management and reducing substance use, as well as barriers they may encounter, strategies they may use, and available social supports. Components will be adapted based on findings from phase 1. Zambian investigators will translate materials into Bemba and Nyanja. The HC adaptation process will involve initial programming in collaboration with the CAB and evaluation of the intervention content and its cultural acceptability through a youth advisory board and beta testing.

##### Developing and Programming MTM

MTM will be developed using phase 1 focus groups and delivered by CIAS to support HIV self-management and substance use reduction. Peer messages will be developed using a cowriting strategy [45]. We will use this collaborative, community-based approach to build the database for this study by including peer messages written by Zambian young people with HIV selected from the focus groups. First, young people with HIV will be asked to describe 3 to 5 factors or situations that have facilitated or challenged their efforts to improve HIV self-management and reduce substance use, as well as strategies used to overcome barriers. Next, for each scenario described, they will be asked to write messages to help other young people with HIV in a similar situation. To ensure coverage of key topics, the co-writing strategy [45] will focus on developing messages that educate and motivate participants regarding HIV self-management, substance use reduction, HIV-related stigma, and other themes identified during the group discussions. Our team will write messages for these topics and ask young people with HIV to rewrite them in their own words, which will then be reviewed by the CAB. MTM will be sent daily for 2 months, followed by weekly for 4 months at a time of the participant’s choosing to promote autonomy and engagement.

##### Prepilot Testing of mHC and MTM

The final step of assessment, decision, adaptation, production, topical experts-integration, training, testing is testing, conducted in 2 steps: theater testing and one-on-one beta testing. In step 1, theater testing pretest methodology172 will be used with the CAB to gauge participants’ reactions to the mHC and MTM components. During theater testing, facilitators will demonstrate excerpts of the mHC sessions and MTM that capture core elements of the intervention. At the end of each excerpt, CAB members will complete brief surveys that contain closed-ended and open-ended questions to elicit their reactions regarding the appropriateness of the elements for the new population. The goal is to collect critiques of the material, content, and delivery and to identify changes that should be included to enhance relevance and efficacy for the target population.

Following modification based on step 1, step 2 will involve systematic one-on-one beta testing over 2 rounds of 5 participants from the target population (10 in total), staggered to allow iterative feedback on technological components and intervention content, followed by refinement. During each round, young people with HIV will complete 4 HC sessions within 2 months, as well as daily MTM between HC sessions. We will also administer baseline and postintervention measures in the beta study to obtain feedback on readability and participant burden. Moreover, 24 hours after the first MTM, staff will call the participant to check for any issues. After completing all mHC sessions, participants will receive an SMS text message prompting them to complete a brief online survey. Participants who do not respond will be contacted by telephone. The survey will collect feedback on technical issues and participants’ experiences with session length, delivery, content, and the receipt and comprehension of MTM. An interview will be conducted after all the sessions are completed to further assess feasibility and acceptability: (1) review technical or other issues in delivering components and (2) solicit input on how to refine delivery and content. mHC and MTM will be modified before round 2, which will follow the same format as round 1. Following theater testing and 2 rounds of beta testing, we expect the refined intervention components to be ready for the pilot trial.

#### Phase 3: Pilot MOST Design–Based Trial

##### Overview

We will evaluate the feasibility, acceptability, and preliminary efficacy of adapted intervention components to improve HIV self-management and substance use in a MOST design–based trial (ClinicalTrials.gov NCT06415357). The design is shown in Table 1. The trial will examine the effect of each component and whether the presence or absence of a component has an impact on the performance of other components. An advantage of the MOST framework is its ability to identify intervention components that make significant contributions to overall effectiveness and should therefore be retained in an optimized intervention package. We will use a full factorial design because of its relative simplicity and cost-efficiency [46]. For our trial, there are 2 components, each with 2 levels, resulting in a 2×2 full factorial design with 4 experimental conditions (Table 1). We will use viral suppression as a measure of success (viral load <200 copies/mL) [47] and optimization criterion. We will enroll 100 young people with HIV who are not adherent to ART and report unhealthy alcohol use [48] or any drug use. “Standard ART counseling” will be provided to all participants as a constant component. Young people with HIV will be randomly assigned to 1 of 4 conditions (Table 1). The primary outcome will be ART adherence and HIV viral load. The main effects of the components and interactions between them will be estimated using ANOVA. The goal of this pilot trial is to estimate preliminary effect sizes, evaluate feasibility and acceptability, and identify promising intervention components for inclusion in a future fully powered RCT. This protocol is developed in accordance with the SPIRIT (Standard Protocol Items: Recommendations for Interventional Trials) guidelines (Multimedia Appendix 1).

**Table 1 table1:** Full factorial design with 4 experimental conditions.

Experiment conditions	Standard antiretroviral therapy counseling	Mobile Healthy Choices	Motivational text messaging
1 (n=25)	Yes	Yes	Yes
2 (n=25)	Yes	Yes	No
3 (n=25)	Yes	No	Yes
4 (n=25)	Yes	No	No

##### Randomization to Conditions

We will use covariate-adaptive randomization [49] to achieve balance on key baseline confounding variables across 4 experimental conditions. Specifically, the project manager will conduct covariate-adaptive randomization after the baseline interview. Key information on participants (eg, gender, substance use behavior, and level of ART adherence) will be extracted at recruitment and will be used as input data for a SAS randomization program created by the UMass Quantitative Methods Core.

### Study Sample

Young people with HIV will be included if they provide informed consent. Inclusion criteria will be as follows: (1) living with HIV and aged between 18 years 0 months and 24 years 11 months; (2) visual analog scale showing <80% medication adherence in the last month and unhealthy alcohol use or any drug use in the last month [50]; and (3) able to understand, read, and speak English, Nyanja, or Bemba. Exclusion criteria are as follows: (1) a serious cognitive or psychiatric problem that would compromise ability to provide informed consent and (2) current enrollment in another HIV intervention study. Smartphone ownership is not required; a smartphone with internet access will be provided at no cost to participants who do not have one.

### Sample Size of the Trial

This pilot MOST design–based trial is designed to estimate main effects of mHC and MTM and their interaction using a 2×2 factorial study design. Using G*Power 3.1.9 (ANOVA procedure), with effect size f=0.35, α=.05, and sample size=100 (25 per condition), statistical power is 80% for detecting main effects of mHC and MTM and 73% for detecting their interaction. Our proposed pilot trial is not an efficacy study, but our sample is large enough to detect a medium to large effect size of mHC and MTM.

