**Primary outcomes**		
	Acceptability	System Usability Scale, Client Satisfaction Questionnaire, and exit interviews
	Feasibility	Retention rate ≥85% at 6-month follow-up, number of responses to SMS text messages, and number of HC^a^ sessions completed
	ART^b^ adherence	Visual analog scale, 4-week percent of doses taken, and DBS^c^ for HIV viral load (viral suppression defined as <200 copies/mL)
	Substance use	ASSIST^d^ and AUDIT-C^e^

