### Data Analysis

We will estimate retention rates overall and per condition and examine differences across conditions using chi-square tests. We will assess differences in acceptability using 2-tailed *t* tests or Mann-Whitney *U* tests. Minimum criteria for acceptability and feasibility will include a mean System Usability Scale score ≥70 and at least 50% of participants responding to MTM at least once and completing at least 2 mHC sessions [51].

To test the main effects and interactions between components using data from the 2×2 factorial study design, we will use ANOVA with effect coding (−1=“no” condition; +1=“yes” condition) rather than dummy coding. The preliminary intervention effects on ART adherence and substance use outcomes will be assessed using linear mixed-effects models, while viral suppression will be analyzed using mixed-effects logistic regression models. Models will adjust for baseline values of the outcome and relevant covariates and will account for repeated assessments over time. Missing data will be handled using full information maximum likelihood estimation. Effect sizes will be estimated for the primary outcomes.

We will make a preliminary selection of components that have achieved main effects. This selection will then be re-evaluated considering any substantial interaction effects to understand how the components work in combination. Depending on the optimization criterion (viral suppression), this will be combined with other information (eg, cost, feasibility, and scalability) to make a final selection of components. This information will inform the development of an optimized intervention package.

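### The stated power (80% main effects, 73% interaction) does not follow from the stated inputs, which give 93.4% for all three effects

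*Protocol article*

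**What the plan says.** The section Sample Size of the Trial says that the pilot is "designed to estimate main effects of mHC and MTM and their interaction using a 2×2 factorial study design". It names the software and test ("Using G*Power 3.1.9 (ANOVA procedure") and gives one set of inputs: "with effect size f=0.35, α=.05, and sample size=100 (25 per condition". From these it reports that "statistical power is 80% for detecting main effects of mHC and MTM and 73% for detecting their interaction". It gives no separate f for the interaction, no numerator degrees of freedom, no attrition allowance and no adjustment of alpha.

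The Overview of Phase 3 fixes the design: "there are 2 components, each with 2 levels, resulting in a 2×2 full factorial design with 4 experimental conditions". Its Table 1 shows 25 participants in each of the four conditions. The Data Analysis section sets the contrasts: "we will use ANOVA with effect coding (−1=“no” condition; +1=“yes” condition) rather than dummy coding".

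**The concern.** Inputs and results are both printed, so the sentence can be checked directly, and two things look wrong. First, 80% is low for f=0.35 with 100 participants and a test on 1 degree of freedom. Second, the interaction is given less power than the main effects, although only one f is stated and all three effects in a balanced 2×2 are tested on the same degrees of freedom.

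This sentence is the article's only quantitative support for the sample size. As it stands, a reader cannot tell whether f, N, the degrees of freedom or the power is wrong. The pilot is also meant to prepare a fully powered trial, so a wrong convention for degrees of freedom, or an f that was not the one used, could be carried forward.

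**Working it through.** **Inputs**
- Design: 2×2 with four cells (Phase 3 Overview and Table 1), so each main effect has 2−1 = 1 numerator degree of freedom and the interaction has (2−1)(2−1) = 1.
- f = 0.35, alpha = .05, N = 100, 25 per cell (Sample Size of the Trial).
- Denominator degrees of freedom: 100 − 4 = 96.

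**Attempt to reproduce the stated figures**

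For a fixed-effects ANOVA, power = P(F′ > F_crit), where F′ is noncentral F with noncentrality λ = f²N.
- λ = 0.35² × 100 = 12.25
- F_crit (1, 96; .05) = 3.94
- Power = 0.934

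The same λ and degrees of freedom apply to mHC, MTM and their interaction, so the result is 93.4% for each. The differences from the article are 93.4 − 80 = 13.4 points and 93.4 − 73 = 20.4 points. Neither figure is reproduced.

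**Cross-checks**
- f = 0.35 for a two-level factor is a standardised difference of 2f = 0.70 between groups of 50 and 50. The normal approximation gives 0.938.
- A simulation of the effect-coded model (40,000 runs) gives 0.933, 0.934 and 0.935 for mHC, MTM and the interaction.

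**Can other settings explain 80% and 73%?**

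| Setting (alpha .05) | Power |
|---|---|
| f=0.35, N=100, numerator df 2 | 0.880 |
| f=0.35, N=100, numerator df 3 | 0.832 |
| f=0.35, N=80, numerator df 1 | 0.871 |
| f=0.35, N=80, numerator df 2 | 0.790 |
| f=0.35, N=80, numerator df 3 | 0.727 |
| f=0.283, N=100, numerator df 1 | 0.800 |
| f=0.260, N=100, numerator df 1 | 0.730 |

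Two routes come close to both figures. One uses N=80 with 2 and 3 degrees of freedom, but the article states no such loss and those degrees of freedom do not fit two-level factors. The other uses two different, smaller values of f, and the article gives neither. Which route was taken, if either, cannot be known from the document.

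**What one f means for the two kinds of effect**

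With −1/+1 coding, a coefficient of f SD moves each cell by ±f.
- Main effect: the two levels differ by 2f = 2 × 0.35 = 0.70 SD.
- Interaction: it adds +2f to the simple effect of one component at one level of the other and −2f at the other level. The difference between simple effects is 4f = 4 × 0.35 = 1.40 SD.

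**Sensitivity figures (not the plan's own assumptions)**
- N=85, numerator df 1, f=0.35: λ = 0.1225 × 85 = 10.41, power 0.890 for each effect.
- An assumed 0.70 SD difference between simple effects: f = 0.70/4 = 0.175, λ = 0.175² × 100 = 3.06, interaction power 0.410 at N=100.

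**The case against.** The strongest defence is that the error is harmless. At the stated f, both printed figures are too low. With 1 degree of freedom, 80% power at f=0.35 needs only about 67 participants, and 100 participants reach 80% power at f of about 0.283. The section's conclusion that the sample can detect a medium to large component effect therefore survives. The article also says that the pilot is not an efficacy study. All of this stands, and it limits the weight of the point, but it does not make the sentence correct.

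A reader might go further and infer any of the following, which the document does not support:
- **That the trial is underpowered for the interaction.** The 41% rests on an effect size chosen for illustration. The article gives no expected interaction size, so neither 0.70 SD nor 1.40 SD can be called plausible or implausible from it. At the stated f, the 73% is understated, as the 80% is.
- **That power should be taken at N=85.** "Retention rate ≥85% at 6-month follow-up" is a feasibility criterion in Table 2 and not an attrition assumption for power. The planned mixed models with full information maximum likelihood also do not restrict the analysis to completers.
- **That the authors used 3 degrees of freedom and 80 participants.** This is a guess from trying settings, and an unreported f fits as well.
- **That the interaction should be estimated and not tested.** The Phase 3 Overview and the Data Analysis section both make the interaction part of the planned analysis, and a wrong power figure is no reason to remove it.

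**Conclusion.** The power statement is wrong as written. Under its own inputs, power is 93.4% for each main effect and for the interaction, and the 7-point gap between the printed figures cannot arise from one f with equal cells. This rests only on the stated f, alpha, N and allocation, and on the 1 numerator degree of freedom that the 2×2 design implies. It needs no assumption from outside the document.

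The consequence is limited. No sample size, allocation, endpoint or criterion is shown to need changing. What is unreliable is the planning record: either the power figures or the inputs printed beside them are not the ones that belong together.

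**What to change.** Make one of two corrections in Sample Size of the Trial:

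1. If the printed inputs are right, replace both figures. Suggested wording: *With 100 participants (25 per condition), f=0.35, alpha .05 and 1 numerator degree of freedom, power is about 93% for each main effect and for the interaction.*
2. If other inputs were used, state the f, N and numerator degrees of freedom behind each figure. With 1 degree of freedom and N=100, for example, 80% belongs to f of about 0.283 and 73% to f of about 0.260.

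In either case, give the SD-scale meaning of the f used. For f=0.35 this is 0.70 SD for a main effect and 1.40 SD between simple effects for the interaction. The authors may add the 89% (N=85) and the 41% (assumed 0.70 SD difference between simple effects) if both are labelled as sensitivity figures.

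The cost is a few sentences and a check of the G*Power output. Design, conduct and the planned interaction test are unchanged.

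### The stated power is for a continuous ANOVA effect, but components are to be chosen on binary viral suppression, where 100 participants detect only differences of roughly 21 to 30 points and no precision is given

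*Protocol article*

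**What the plan says.** **Sample size.** The section Sample Size of the Trial reads "Using G*Power 3.1.9 (ANOVA procedure"), "with effect size f=0.35, α=.05, and sample size=100 (25 per condition"), and reports that "statistical power is 80% for detecting main effects of mHC and MTM and 73% for detecting their interaction". It names no outcome. It adds that "Our proposed pilot trial is not an efficacy study" but that "our sample is large enough to detect a medium to large effect size of mHC and MTM".

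**Decision criterion.** The Phase 3 Overview states: "We will use viral suppression as a measure of success (viral load <200 copies/mL) [47] and optimization criterion".

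**Analysis and selection.** Data Analysis tests main effects and the interaction by ANOVA with effect coding. It uses linear mixed models for ART adherence and substance use, while "viral suppression will be analyzed using mixed-effects logistic regression models". It then says: "We will make a preliminary selection of components that have achieved main effects". That selection is re-evaluated for interactions and combined, in light of the viral suppression criterion, with cost, feasibility and scalability. Achieving a main effect is not defined.

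**Retention.** Table 2 sets a target of at least 85% at 6 months. The sample-size section makes no allowance for dropout.

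**The concern.** Cohen's f in a fixed-effects ANOVA describes a continuous outcome, so the only sensitivity statement in the protocol does not describe the outcome that drives the choice of components. Two things are at stake.

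- A reader may take the sample as adequate for ranking components on viral suppression without seeing how wide the uncertainty is.
- If the first selection step is a significance screen, a component with a moderate benefit could fail it through lack of precision. Data Analysis describes no explicit route back for such a component.

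There is also a question of scale. A mixed-effects logistic model gives a subject-specific odds ratio, which lies further from 1 than the population effect. Component choice and planning of the next trial need the population effect.

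**Working it through.** **1. The plan's own figure.** Inputs from Sample Size of the Trial: f = 0.35, α = .05, N = 100, four cells of 25. In a balanced 2×2 design each main effect and the interaction has 1 numerator df, with 96 error df.

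- Noncentrality λ = f² × N = 0.1225 × 100 = 12.25. Critical F(1, 96) = 3.94.
- Power = P(noncentral F > 3.94) = 93.4%, the same for main effects and interaction.
- With 2 or 3 numerator df, power is 88.0% or 83.2%. At N = 100 and 1 df, 80% power corresponds to f = 0.283 and 73% to f = 0.260.
- The closest joint match is N = 80 with 2 df (79.0%) and 3 df (72.7%), but the protocol states neither that N nor those df.

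So 80% and 73% do not follow from the stated inputs, and they cannot differ at the same f.

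**2. Binary main effect, one visit.** There are n = 50 per factor level, or 42.5 at 85% retention. The test is two-sided at .05. Comparator rates p₀ of 30–60% are assumed.

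Power = Φ[(d − 1.96 × SE₀)/SE₁], with SE₀ = √(2p̄(1−p̄)/n), where p̄ is the mean of p₀ and p₁, and SE₁ = √((p₀(1−p₀) + p₁(1−p₁))/n).

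Example, 50% versus 65% at n = 50: SE₀ = √(2 × .575 × .425/50) = .0989 and SE₁ = √((.25 + .2275)/50) = .0977. Then (.15 − 1.96 × .0989)/.0977 = −0.45, and power is 33%.

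| Comparator | 30% | 40% | 50% | 60% |
|---|---|---|---|---|
| Detectable difference at 80% power, n = 50 (points) | 27.5 | 27.6 | 26.7 | 24.8 |
| Same, n = 42.5 (points) | 29.8 | 29.8 | 28.7 | 26.5 |
| Power for +15 points, n = 50 | 34% | 32% | 33% | 36% |
| Same, n = 42.5 | 30% | 28% | 29% | 31% |
| Power for +20 points, n = 50 | 53% | 52% | 53% | 59% |
| Same, n = 42.5 | 47% | 45% | 47% | 52% |

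At a 70% comparator the detectable difference falls to 21.8 points (23.2 at 85% retention).

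The 95% CI half-width near 50% is 1.96 × √(2 × .25/50) = 19.6 points, or 21.3 at n = 42.5.

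**3. Two visits.** Viral load is planned at 3 and 6 months. Assume the same effect at both visits and a within-person correlation ρ. Averaging the visits multiplies both SEs by √((1+ρ)/2).

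- Detectable difference for ρ = 0.4–0.8: about 21–26 points at n = 50 and 23–28 at n = 42.5.
- Power for ρ = 0.3–0.6, over both values of n: about 34–51% for +15 points and 54–78% for +20.

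**4. Miss rates if a significance screen applied.** The miss rate is 1 − power. With two visits it is 49–66% for +15 and 22–46% for +20. With one visit it is 64–72% and 41–55%.

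**5. Is the quoted sentence false on the binary scale?** Cohen's h = 2·arcsin√p₁ − 2·arcsin√p₀. For the detectable 25–28 points, h is about 0.56–0.57, which is medium to large.

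**6. Illustrative estimate-based rule.** Keep a component if its estimated risk difference is at least 10 points (n = 42.5, one visit).

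- Inert component: SE = √(2p₀(1−p₀)/42.5) = .099–.108, so P(estimate ≥ .10) = 16–18%.
- True +15 from 50%: SE = .106, (.10 − .15)/.106 = −0.47, kept 68% of the time. Significance at the same n keeps it 29% of the time.

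**The case against.** The strongest reply is that the protocol states no significance rule. The selection wording gives no p-value, the step is called preliminary, and interactions, cost, feasibility and scalability follow. The stated goal is to estimate effect sizes and find promising components. The Overview does speak of components that contribute significantly, but as a general advantage of the framework. This stands. A reader might infer that the plan will usually discard a useful component. The document supports neither the rule nor a definition of useful, and with two visits a 20-point gain would be detected more often than not under these assumptions.

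Repeated visits and baseline adjustment also add precision. The two-visit gain is counted above. The gain from baseline adjustment is not, because nothing in the document allows it to be sized.

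Three other stronger readings are tempting and do not hold.

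- **That the quoted sentence is false.** On the binary scale the detectable effect is still medium to large. The fault is that the sentence is not tied to the criterion.
- **That the interaction is far worse powered.** Near 50%, a difference-in-differences needs 2.80 × √(4 × .25/25) = 56 points. Under the planned −1/+1 coding the interaction contrast is half of that, 28 points, and as precise as a main effect. The gap is one of scale.
- **That the next trial will be undersized.** No text says a subject-specific odds ratio will be used as a population effect. The gap between the two depends on a random-intercept variance that the document does not give.

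Exact thresholds and marginal standardisation may sit in an analysis plan that is not shown. The mismatch between the power statement and the criterion, and the figures that do not reproduce, are in the article itself.

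**Conclusion.** The point holds as a mismatch with a measurable size. The protocol supports its sample size with a continuous-outcome calculation and decides on a binary one. For that outcome, 100 participants detect about 25–28 points from one visit (27–30 at 85% retention), and roughly 21–28 when two correlated visits are averaged. This rests on assumed comparator rates of 30–60%, two-sided α of .05, a constant effect over visits and no credit for baseline adjustment.

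The miss rates, half to two-thirds for +15 points and a quarter to half for +20, are conditional on reading the selection step as a significance screen, which the protocol does not state. Without that reading the step is undefined and still needs wording.

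The finding that the stated inputs give 93.4% rather than 80% and 73% needs no assumption beyond those inputs and the 2×2 design. Being a pilot does not remove the point, because estimating effects is the stated aim and precision is what that aim needs.

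**What to change.** 1. **Restate the sample-size paragraph.** Correct the ANOVA power or the inputs behind it, and say that it applies to continuous outcomes. Add the detectable difference and the expected 95% CI half-width for viral suppression (about ±20 points near 50%, one visit), with the assumed suppression rate and retention.
2. **Report on the population scale.** Give each component's effect on suppression as a model-standardised marginal risk difference with 95% CI, alongside the odds ratio from the mixed model.
3. **Define the preliminary selection.** Base it on the estimated risk difference and its CI against a minimum set in advance by the investigators, not on significance. The 10-point figure above is only an illustration.

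The cost is wording and one post-estimation step. The stated precision for the key outcome will look worse. An inert component will be carried forward more often, about 16–18% of the time in the illustration, and a true 10-point component would be kept only half the time. The later RCT is there to catch an inert component that is carried forward.
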